### Design

2.6

This is a controlled, randomized, single-blind clinical trial:

G1 – (experimental group -PDT) 20 patients with halitosis, 1 session of PDT will be performed with the PS. PS will be applied in enough quantity to cover the middle third and back of the tongue and wait for 5 minutes. The irradiation will be performed with low intensity laser λ = 660 nm, in 6 points, 9 J per point and radiant exposure of 318 J/cm^2^.G2 – (positive control group - tongue scrapper) 20 patients with halitosis treatment tongue scraping will be performed by the same operator. Posterior-anterior movements will be performed with the scraper over the lingual dorsum in order to promote the mechanical removal of tongue coating.

### Methodology for irradiation – low level laser specifications and dosimetry

2.7

All participants of G1 group will be submitted to the application of 0.005% methylene blue (Chimiolux 5, DMC, São Carlos, São Paulo) in enough quantity to cover the middle and posterior third of the of the dorsum of the tongue with a pre-irradiation time of 3 minutes. Will be performed irradiations with the red laser diode (λ = 660 nm) with output power of 100 mW, 9 J, 318 J/cm^2^ and irradiance of 3537 mW/cm^2^ with a point application method and in direct contact with the tongue (Therapy XT, DMC, São Carlos, SP, Brazil).^[18,19]^ The irradiations will be done in 6 points with a distance of 1 cm between the points, considering the scattering halo and the effectiveness of PDT (Fig. 1). To completely remove the dye, the tongue will be washed in abundance with saline solution. During the laser application both patient and operator will wear goggles.

**Figure 1 F1:**
[figure not shown]
Photodynamic therapy- Photosensitizer and irradiation points of laser.

### Treatment with tongue scraper

2.8

All participants of G2 group will receive treatment with tongue scraper as described below: the lingual scraper will be positioned on the posterior dorsum of the tongue, in the region of the valved papillae, and will pull with slight pressure to the apex of the tongue, obeying the manufacturer's instructions. This procedure will only be performed once.^[26]^

### Periodontal treatment and oral hygiene guidance

2.9

After the treatment on the back of the tongue a new evaluation of VSC by gas chromatography (OralChroma, Abilit, Japan) and new collection for microbiological analysis of all patients of both groups will be performed.

Periodontal treatment will be performed, removing in a single session, all biofilm and calculus with universal curettes (Hu-Friedy, Chicago, IL) and ultrasonic device (EMS-Piezon Systems PM200, Nyon, Switzerland), by an experienced and specialist investigator. All participants will receive oral hygiene guidance (HBO). After periodontal treatment of these patients, the VSC will be evaluated and the microbiological collection will be repeated.

### Outcome measures

2.10

#### Halitosis measurement (gas chromatography test)

2.10.1

The portable Oral Chroma (Abilit, Japan), a sensitive semiconductor gas sensor, will be used for the assessment of halitosis. Oral air collection will follow the manufactured guide lines (Oral Chroma Manual Instruction). A syringe will be placed in the patient's mouth with the plunger completely inserted and the participant will breathe through the nose with the mouth closed for 1 minute. The plunger will then be withdrawn to fill the chamber with air. The gas injection needle will be placed on the syringe and the plunger will be adjusted to 0.5 ml. This air will be injected into the input of the device in a single motion (Fig. 2). There is a software that produces a graph and stores at the device the values of concentration of VSCs (from 0 to 1000 ppb). Values above 112 ppb are indicators of halitosis. This procedure will be performed always in the morning and participants will receive a list of products to be avoided or forbidden, as spices, alcohol, coffee and chewing gums. The halitosis measurement will be done several times: before, after PDT or scraper, after periodontal treatment, after 1 week and 3 months later.

**Figure 2 F2:**
[figure not shown]
Oral Chroma Device (Abilit, Japan), VCS results.

#### Microbiological analysis

2.10.2

Sampling will be performed on the back of the tongue before and after halitosis treatment, after 1 week and 3 months later. Samples of the tongue coating will be collected with swab, placed in sterile identified microtubes (containing Tris-EDTA) and stored at -80oC until analyzed. After thawing, the samples will be vortexed for one minute. DNA extraction will be performed with the Master Pure DNA Extraction Kit (Epicenter Technologies Corp., Chicago, IL) according to the manufacturer's instructions. The purified DNA will be resuspended in TE buffer. The quantitative analysis will be performed using the Step One Plus Real-Time PCR System (Applied Biosystem, Foster City, CA) and the products detected by fluorescence using the Quantimix Easy SYG Kit (Biotools, Madrid, Spain) by the manufacturer. For the reaction, 10 μl of SYBR Green, 0.5 μl DNA template, 200 mM of each primer corresponding to the genes specific for identification of *T. denticola*, will be used.^[27]^

#### OHIP

2.10.3

*Analysis of Oral Health Impact Profile* (OHIP-14 questionnaire): The OHIP-14 is an instrument that consists of 14 items, arranged in 7 domains among the following subscales: functional limitation, pain, psychological discomfort, physical disability, psychological disability, social disability and social handicap. The answers are given corresponding to a total of 5 points on a Likert-type scale. The scale included the following responses: never (coded 0), hardly ever (coded 1), occasionally (coded 2), fairly often (coded 3), and very often (coded 4). The OHIP-14 scale ranged from 0 to 56, with higher scores indicating poorer QoL.^[28]^ Oral health related to quality of life (OHRQoL), will be assessed by Brazilian version of OHIP-14 questionnaire.^[29]^ A calibrated examiner will apply the OHIP-14 on the day that the patient history is taken, (baseline) and 3 months after the treatment for halitosis. The items of the OHIP-14 are shown in Table 1.

**Table 1 T1:**
[figure not shown]
Ohip-14 questionnaire and its domains.^[28]^.

A flowchart is presented for an overview of the study (Fig. 3).

**Figure 3 F3:**
[figure not shown]
Flowchart presenting an overview of the study.

### Statistical analysis

2.11

The normality of the data will be determined by the Lilliefors test. If normality is demonstrated, analysis of variance (*t* test Student, Bioestat 5.3, Pará, Brazil) will be used to compare continuous and dependent variables among the groups (G1 and G2). Mann–Whitney test will be used if non-normal distribution is demonstrated. The data collected at 1 week evaluation will be contrasted to the baseline data. A *P* value < .05 will be considered indicative of statistical significance. The *x*^2^ test will be used to compare categorical variables among G1 and G2, at baseline and the 1 week evaluation. These data will be expressed as mean ± standard deviation.

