**Lessons::**

This protocol will determine the effectiveness of phototherapy regarding the reduction of halitosis in adults. clinicaltrials.gov NCT 03996915.

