## Methods

2

A single-center, randomized, controlled, single-blind clinical trial was designed in accordance with the criteria recommended for interventional trials in the SPIRIT statement. The protocol was approved by the Research Ethics Committee of Nove de Julho University (UNINOVE), number # 3.257.104 and registered at clinicaltrials.gov NCT 03996915. The study is in accordance with the *Declaration of Helsinki*. Patients who accept to participate will sign the Informed written consent form after verbal and written explanation of the study.

All data collected and laboratory samples will be identified and maintained confidential. Only the main investigators (authors of this article) will have complete access to the set of clean data.

The sample will comprise of 40 older adults’ patients (50 years or older) with halitosis. After agreeing to participate, patients will be evaluated in different moments: baseline- before halitosis treatments (T0), immediately after halitosis treatment (T1), after periodontal treatment (T2), after 1 week (T3) and three months later (T4). The clinical assessment and the PDT treatment will be performed by the same researcher, in all 4 moments at the Dental Clinic at Nove de Julho University – UNINOVE, São Paulo, Brazil, from September 2018 until March 2019. The measurements were performed by another researcher, who does not know the nature of treatments.

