### Inclusion and exclusion criteria

2.2

Participants in this study will be evaluated to meet the eligibility criteria: both genders, with at least 10 teeth, PSR 0, 1 or 2, without any changes in the anatomy of the back of the tongue (geographical or fissured tongue) and positive halitosis (SH2 level higher than 112 ppb).

The following patients will be excluded: smokers or ex-smokers for less than 5 years and patients with hypersensitivity to the photosensitizer (PS).

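### The 1-week versus baseline contrast is undefined: tested within an arm, it could credit PDT with regression to the mean and shared co-treatment, while the randomised test leaves baseline SH2 unused

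*Protocol article*

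**What the plan says.** All references are to the protocol article.

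- **Entry (section 2.2).** Patients must have "positive halitosis (SH2 level higher than 112 ppb".
- **Outcome (section 2.10.1).** The same variable is measured with OralChroma against the same cut-off: "Values above 112 ppb are indicators of halitosis".
- **Visits (Methods).** Patients are assessed at "baseline- before halitosis treatments (T0), immediately after halitosis treatment (T1), after periodontal treatment (T2), after 1 week (T3) and three months later (T4".
- **Shared care (section 2.9).** Single-session periodontal treatment and hygiene guidance follow the tongue treatment in both groups, before the 1-week visit.
- **Group tests (section 2.11).** Student's t test "will be used to compare continuous and dependent variables among the groups (G1 and G2"; otherwise, "Mann–Whitney test will be used if non-normal distribution is demonstrated". No baseline covariate is named. For categorical data the chi-square "test will be used to compare categorical variables among G1 and G2, at baseline and the 1 week evaluation".
- **Contrast over time (section 2.11).** "The data collected at 1 week evaluation will be contrasted to the baseline data". The P < .05 rule comes next. No test is tied to this contrast, and the text does not say whether it is within or between groups.
- **Intended claim (Abstract, Lessons).** "This protocol will determine the effectiveness of phototherapy regarding the reduction of halitosis in adults".

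**The concern.** Patients selected for a high value of a variable that fluctuates will on average read lower when measured again, even if nothing is done. Entry and outcome here are the same SH2 reading scale with the same 112 ppb line, so a fall from baseline to 1 week is expected without any treatment effect. Periodontal treatment and hygiene guidance come between the two readings in both arms, so a within-arm fall also contains their effect.

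A within-arm reading is a natural one for this trial. The Introduction motivates the study by a pre-post finding, that halitosis was back at its baseline level after 7 days. The comparator is active, and the Discussion calls both treatments effective. If the arms do not differ, the fall from baseline is what remains to support a claim that PDT works. A second route to a false claim is a significant fall in one arm and not in the other, read as a difference between treatments.

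Separately, the randomised comparison is specified without the baseline SH2 value that every patient has, which gives away precision in a trial of 20 per group.

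**Working it through.** **Inputs from the document:** threshold 112 ppb (2.2, 2.10.1); 20 per group, 1:1 (Abstract, 2.5); significance at P < .05, taken as two-sided (2.11). The plan gives no figure on this point to reproduce.

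**Assumed inputs (not in the document):** log-normal SH2 in screened people, median 90–150 ppb, log-SD σ 0.6–0.9, test-retest correlation ρ 0.5–0.85, no treatment effect, and the entry reading serving as baseline. The device range limit at 1000 ppb is ignored.

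**1. Expected fall with no effect.** With c = (ln 112 − ln median)/σ and λ = φ(c)/(1 − Φ(c)), the mean fall on the log scale is (1 − ρ)·σ·λ.

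- Median 90, σ 0.9, ρ 0.5: c = 0.243, λ = 0.959; fall = 0.5 × 0.9 × 0.959 = 0.432, so the geometric mean drops by 1 − e^(−0.432) = 35%.
- Median 150, σ 0.6, ρ 0.85: c = −0.487, λ = 0.516; fall = 0.15 × 0.6 × 0.516 = 0.046, a drop of about 5%.

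Over the whole range the geometric mean falls 5–35%, and 11–43% of patients drop below 112 ppb.

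**2. How often a within-arm test would be significant.** Simulated trials with n = 20 and no effect:

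- Paired t test on log SH2 shows a significant fall in about 9% (median 150, σ 0.6, ρ 0.85) to 70% (median 90, σ 0.6, ρ 0.5) of trials.
- One arm is significant and the other not in about 17–50% of trials.
- An independent run under a normal model (ρ 0.5–0.9, 30–50% of screened people above the threshold) gives 12–78% and 21–50%.

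**3. The randomised comparison.** In the normal-model null trials, G1 versus G2 rejects in 4.7–5.3% of trials, whether on the unadjusted 1-week value, on change, or by ANCOVA. Bias is under 0.003 SD.

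**4. Precision left unused.** The ratio of ANCOVA variance to that of a test on the 1-week value alone is 1 − r², where r is the baseline/1-week correlation among enrolled patients. Selection shrinks r. With k = 1 + cλ − λ², r² = ρ²k/(ρ²k + 1 − ρ²).

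- Median 90, σ 0.6, ρ 0.5: c = 0.364, λ = 1.043, k = 0.291; r² = 0.073/(0.073 + 0.75) = 0.09; ratio 0.91, equivalent to 20/0.91 ≈ 22 per group.
- Median 150, σ 0.6, ρ 0.85: k = 0.483; r² = 0.349/(0.349 + 0.2775) = 0.56; ratio 0.44, equivalent to 20/0.44 ≈ 45 per group.

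In power terms, for a true difference of 0.6 screening-population SD with 30% above the threshold, unadjusted versus ANCOVA is 54% versus 56% (ρ 0.5), 64% versus 72% (ρ 0.7) and 84% versus 99% (ρ 0.9).

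**The case against.** Three stronger readings are tempting, and the document supports none of them.

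- **That the unadjusted group test lets regression to the mean look like benefit.** It does not. Both arms are randomised under one entry rule, so the expected fall is the same in each and cancels. Leaving baseline out costs precision and leaves chance imbalance uncorrected; it does not bias the comparison.
- **That the treatment effect is read from 1 week versus baseline.** Section 2.11 plans group comparisons first. The baseline sentence could mean a between-arm comparison of change, which would respect the pairing and be valid. The text does not settle it.
- **That a single high reading qualifies the patient.** Section 2.2 does not say how many readings are taken or whether the qualifying one is T0. A separate T0 reading would already absorb much of the fall.

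It is also fair to say that 2.11 names no paired test, and an unpaired test on positively correlated readings is generally more conservative, so the 9–70% applies only if a paired within-arm test is run. All SH2 inputs are assumed, and the range runs from a minor problem to a major one. Baseline adjustment is often left to an analysis plan, and none is shown, so its absence alone would not be a finding.

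On shared care, the Discussion words periodontal treatment as being for patients whose halitosis persists, whereas 2.9 reads as covering everyone. On neither wording is it confined to the PDT arm.

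What stands: the baseline contrast is stated, is left undefined, sits beside a significance rule, and is unsafe on one of its two natural readings. The group test that is stated can be improved at almost no cost with data already collected.

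**Conclusion.** The concern holds in a limited form. If the 1-week versus baseline contrast is tested within arm, a significant fall cannot be attributed to PDT: with no effect at all it would appear in about 9–70% of trials under the assumed median, spread and correlation. Shared periodontal treatment and hygiene guidance would add to it. The direction follows from the entry rule, provided the entry reading serves as baseline; the size rests on assumptions. The randomised G1 versus G2 test is valid at about 5% error and is only less precise than it could be. The gain from adjustment is small if the correlation is low and large if it is high. Severity: should-fix.

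**What to change.** Revise section 2.11 as follows.

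- State that any effectiveness claim rests on G1 versus G2 at 1 week.
- Analyse that comparison by ANCOVA of log SH2 (for example log(SH2 + 1), so that zero readings can be used) on arm and log baseline SH2. Report a ratio of geometric means with its 95% CI, with a rank-based ANCOVA as a check in case many readings sit at the device limits of 0 or 1000 ppb.
- Replace the sentence on contrasting 1-week with baseline data by one saying that within-arm change is reported descriptively, without P values or effectiveness claims.
- State whether the qualifying SH2 reading is also the T0 value.

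The cost is a few sentences. Baseline SH2 is already measured, and no visit or patient is added. The one drawback is that a log-scale ratio is slightly less familiar to readers than a difference in ppb.

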## Discussion

3

PDT for the treatment of halitosis is known by causing immediate effects results in an unpleasant odor that emanating from the mouth.^[18]^ However, one study shows halitosis returns in a week after treatment with PDT.^[8]^

Probably, bacteria residing in the periodontal sulcus could recolonize the dorsum of the tongue, therefore we design this study promoting a complete mouth cleaning at once, in order to verify 1 week and 3-month follow-up. We think that immediate effects of PDT should be prolonged by complete one session decontamination of the mouth, by periodontal treatment.

Treatment of halitosis can be done in several ways, including chemical reduction of microorganisms with mouthwashes (chlorhexidine 0.012%, essential oils and triclosan), mechanical reduction with a tongue scraper, masking of the odor (chewing gum, spray, and tablets).^[3]^ However, these treatments may present disadvantages, such as excessive excoriation of the tongue surface with transudation and desquamation, worsening halitosis and causing discomfort when eating acid or bitter foods.^[8]^

PDT has been shown good results in treating halitosis,^[18,19]^ there are no reports of adverse effects or toxicity.^[20,22,30,31]^ As control, will be used a comparative group that will be treated with lingual scraper, the most conventional therapy in the treatment of halitosis.^[8]^

Patients with changes in the anatomy of the back of the tongue (geographical or fissured tongue) will not be included in the study. The fissures and modified papilla may favor the bacterial accumulation predisposing halitosis.^[32]^ Smokers and newly ex-smokers will be excluded, because the air exhaled by them can be mistaken for halitosis.^[33]^ Participants will be randomized in 1:1 equivalence group because both treatments are effective, and we do not expect adverse effects. Also, we decide to block the sample in 5 blocks of 4 patients, because of equivalence in the number of patients in both groups in case of we decide to include 1 more group. We expect a higher drop out because halitosis is a slight health problem and we expect some difficult to convince them to realize 2 follow up. When we achieve 8 patients per group, we will decide for a third treatment group.

It is not possible that this study becomes double-blind study, because patient will always know which therapy is being performed, since lingual scraper and PDT are completely different treatments. However, we planned a blind operator (who will collect OHIP questionnaires, microbiological analyses and VSC by gas chromatography) because he will not know the nature of treatments.

The diagnosis of halitosis will be done using OralChroma, since it is an effective and objective method which is possible to measure the halitosis intensity based on gas chromatography.^[3,14,15]^

Halitosis has also been linked to the presence and severity of periodontal diseases. Studies have shown that concentrations of VCS increase (mainly methyl mercaptan) in patients with periodontal disease, (probing > 4 mm), but it has not been studied to date if periodontal treatment is able to reduce the halitosis of these patients.^[6,16,17]^ Based on this information, in this study, patients who present halitosis even after PDT or tongue scraper treatment will undergo periodontal treatment in our study.

Microbiological analysis will be another outcome measure in this study. The presence of *Treponema denticola* will be assessed since recent studies show that these species are very prevalent in cases of halitosis.^[10–13]^ An accepted theory is that aspiration of oral bacteria could cause or exacerbate systemic disease.^[34–37]^ Based on this theory, it is important to reduce bacterial load.

A valid measure of the halitosis impact on quality of life, is required for the assessment of treatment effectiveness. The HALT (halitosis associated life quality test) questionary is also very useful for reliable results.^[38]^ This tool can immensely help monitoring one's treatment progress, but we still do not have a version for Brazil, that is the reason why we chose OHIP.

The specifications and dosimetry of laser in this search will be the same used in studies that used PDT to treat halitosis and obtained good results. Irradiations with the red laser diode (λ = 660 nm) with output power of 100 mW, 9 J, 320 J/cm^2^ and irradiance of 3537 mW/cm^2^ with a point application method and in direct contact with the tongue, 6 points with a distance of 1 cm between the points, showed significantly reduce of the halitosis levels.^[18,19,8]^

We expect that this randomized, single blinded, controlled clinical trial will be able to treat oral halitosis in healthy adults.

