**Interventions::**

The participants (n = 40) with halitosis will be randomized into 2 groups: G1-treatment with PDT (n = 20) or G2-cleaning of the tongue with a tongue scraper (n = 20).

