### Randomization

2.5

An external researcher who will not participate in this study will perform randomization through the Microsoft Excel program, version 2017. The same researcher will randomize into 5 blocks with 4 patients (1:1) and groups will be designated as A or B. The letters (A or B), drawn will be placed into opaque envelopes labeled with sequential numbers. The envelopes will be sealed and remain in the same numerical order in a safe place until treatments. This data will only be revealed after statistical analysis. As the study will be performed in a single-blinded manner, the operator will not know which kind of treatment will be performed. The patient will not be blinded because the nature of treatments (PDT and tongue scrapers).

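### A third-arm decision at 8 patients per group has no stated basis and conflicts with the fixed two-arm, 20-per-group design; if used, it leaves the error rate uncontrolled

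*Protocol article*

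**What the plan says.** The option appears only in section 3 (Discussion): "When we achieve 8 patients per group, we will decide for a third treatment group". The same paragraph gives it as part of the reason for blocking the sample: "because of equivalence in the number of patients in both groups in case of we decide to include 1 more group". The sentence just before the trigger is about expected drop-out and the difficulty of securing two follow-up visits.

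The rest of the article describes a fixed two-arm trial. The Abstract (Interventions) and section 2.6 (Design) give 40 patients, 20 to PDT and 20 to the tongue scraper. Section 2.5 (Randomization) says "The same researcher will randomize into 5 blocks with 4 patients (1:1) and groups will be designated as A or B", and of the allocation code it says "This data will only be revealed after statistical analysis". Section 2.11 (Statistical analysis) names tests that "will be used to compare continuous and dependent variables among the groups (G1 and G2)", with one threshold: "A *P* value < .05 will be considered indicative of statistical significance".

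The article does not name the third treatment, the grounds for adding it, who decides, the new allocation ratio, the new total or the comparisons to be made.

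**The concern.** The article fixes the timing of a mid-trial design decision but not its grounds. That is more than detail deferred to another document, because the text announces a possible change that the rest of the article does not allow for. The sample size, the A/B list and the G1-versus-G2 tests are all written for two arms.

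Three things are at stake if the arm is opened:

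- **Error rate.** Three groups allow three pairwise comparisons, and the only rule shown is a single 5% threshold.
- **Bias.** A decision taken after seeing outcomes by group would make the design depend on the data.
- **Precision and comparability.** If the total is not raised, G1 and G2 each lose patients. Anyone treated before the third arm opens is not a concurrently randomised control for it.

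**Working it through.** **Inputs from the article.** Total 40, 20 per group (Abstract; section 2.6). Blocks: 5 of 4, 1:1, labels A or B (section 2.5). Trigger: 8 per group (section 3). Significance level 0.05, sidedness not stated (section 2.11).

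**Assumptions.** The effect size formula and resulting sizes in section 2.1 are not shown, so the planned 20 per group cannot be reproduced. I use two-sided 5% and 80% power as a reference, with a two-sample t test.

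**1. Position of the decision.** 8 + 8 = 16 patients, which leaves 40 − 16 = 24. Also 16 / 4 = 4, so the decision falls after exactly four complete blocks.

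**2. Block count.** 5 × 4 = 20 patients. The planned 40 need 40 / 4 = 10 blocks. As written, the list runs out halfway through the trial, and only four places would remain after the decision point.

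**3. Group sizes if a third arm opens.** The article fixes neither the total nor the split, so three cases are shown:

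| Case | G1 / G2 / third | Total |
|---|---|---|
| Last 24 split 1:1:1 (24 / 3 = 8) | 16 / 16 / 8 | 40 |
| Total kept, arms made about equal (40 / 3) | about 13 each | 40 |
| Patients added to keep 20 per arm | 20 / 20 / 20 | 60 |

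**4. Detectable difference, G1 versus G2.** With n per group, df = 2n − 2 and noncentrality d√(n/2). I solve for the d (in SD) that gives 80% power.

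| n per group | Detectable d | Power at d = 0.909 |
|---|---|---|
| 20 | 0.909 | 80% |
| 16 | 1.024 | 70% |
| 13 | 1.145 | 60% |

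For n = 20 the noncentrality is 0.909 × √10 = 2.87; for n = 16 it is 1.024 × √8 = 2.90. In the 60-patient case G1 versus G2 keeps n = 20 and loses nothing. In the 16/16/8 case, the third arm against 8 concurrent controls has n = 8 per side and needs 1.51 SD.

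**5. Type I error.**

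- Arm added without regard to outcomes, G1 versus G2 tested once at 5%: about 0.050 (simulated).
- Three pairs each tested at 5%: 1 − 0.95³ = 0.143 if they were independent. Pairs share arms, and simulation gives about 0.12, both for equal arms and for 16/16/8.
- Two comparisons against a common control: 1 − 0.95² = 0.0975 if independent; about 0.090 by simulation.
- G1 versus G2 tested at 8 and again at 20 per group, with success claimed on either: about 0.088.
- An illustrative rule in which the result at 8 per group sets the final size at 13 or 20: 0.040 to 0.060, depending on the direction of the rule.

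**The case against.** The strongest defence is that this is a contingent remark in the Discussion, while the Methods and analysis are two-arm throughout. Its place beside the drop-out sentence suggests a decision driven by recruitment, and section 2.5 keeps the code closed until after analysis. Multiplicity rules and the choice of controls are often left to an analysis plan, which is not shown here.

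Much of this limits the point. Several stronger readings might be inferred, and the documents do not support them:

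- **That the final P values become uninterpretable.** No section says outcomes are examined at 8 per group. If they are not, the single G1-versus-G2 test stays at about 5%. Even the illustrative outcome-driven size rule moved it only to between 4% and 6%.
- **That the option necessarily breaks the 20-per-group design.** This holds only if the total stays at 40, which the article does not say.
- **That blocks of 4 fail because 4 is not divisible by 3.** The Discussion ties the blocks to equality of the two existing groups, and 16 patients is exactly four complete blocks. Nothing says a third arm would be allocated inside them.
- **That the new arm will be compared with patients treated before it opened.** The article does not say which controls would be used.

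The defence does not remove the core of the point. The recruitment reading is plausible but not stated. The concealment sentence does not clearly bar a look by group. Patients know their treatment, section 2 has one researcher doing both the clinical assessment and the PDT, and section 2.6 has scraping done by the same operator, so the treating researcher must know the groups. A masked comparison of A with B would not be excluded either. The conflict with the two-arm text lies within the article itself, whatever an analysis plan may add.

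**Conclusion.** The point holds in conditional form. The Discussion commits the team to a design decision at 16 patients with no stated basis, against a design, list and analysis that are fixed for two arms.

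If the option is used as it stands, nothing in the article controls the error rate. The size is about 12% family-wise, assuming all three pairs are each tested at 5%. There is also room for bias if outcomes by group inform the decision, which the article neither states nor rules out.

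The loss of power depends on the total. At an assumed 80% power and two-sided 5%, the detectable G1-versus-G2 difference goes from 0.91 to 1.02 SD if the last 24 of 40 patients are split 1:1:1. It is unchanged if recruitment is extended to keep 20 per arm. If the option is never used, none of these effects arises.

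The block count is a separate error that stands in any case: the stated list covers half of the planned patients.

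**What to change.** Preferred: delete the third-arm sentence and the related part of the block rationale from the Discussion, and keep the trial two-arm to 20 per group. The cost is an edit to two sentences and the loss of an option the article never defines.

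If the option is kept, state the following before patient 16, since a rule written later cannot be shown to be independent of the data:

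- the decision uses recruitment counts only, with no outcome seen by group;
- a new three-arm randomisation list and a new stated total apply from that point;
- the new arm is compared only with patients randomised concurrently with it;
- the pairwise tests are Holm-adjusted.

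This version costs more: a protocol amendment, 60 patients rather than 40 if 20 per arm is to be kept, and more still if the third arm is to have 20 concurrent controls per comparison.

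In either case, correct the block count in section 2.5 and the Discussion to 10 blocks of 4. Deleting the third-arm text alone would leave that error in place.
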